## Abstract

**Background:**

The diagnosis of ventilator-associated pneumonia (VAP) remains time-consuming and costly, the clinical tools lack specificity and a bedside test to exclude infection in suspected patients is unavailable. Breath contains hundreds to thousands of volatile organic compounds (VOCs) that result from host and microbial metabolism as well as the environment. The present study aims to use breath VOC analysis to develop a model that can discriminate between patients who have positive cultures and who have negative cultures with a high sensitivity.

**Methods/design:**

The Molecular Analysis of Exhaled Breath as Diagnostic Test for Ventilator-Associated Pneumonia (BreathDx) study is a multicentre observational study. Breath and bronchial lavage samples will be collected from 100 and 53 intubated and ventilated patients suspected of VAP. Breath will be analysed using Thermal Desorption – Gas Chromatography – Mass Spectrometry (TD-GC-MS). The primary endpoint is the accuracy of cross-validated prediction for positive respiratory cultures in patients that are suspected of VAP, with a sensitivity of at least 99% (high negative predictive value).

**Discussion:**

To our knowledge, BreathDx is the first study powered to investigate whether molecular analysis of breath can be used to classify suspected VAP patients with and without positive microbiological cultures with 99% sensitivity.

**Trial registration:**

UKCRN ID number 19086, registered May 2015; as well as registration at www.trialregister.nl under the acronym ‘BreathDx’ with trial ID number NTR 6114 (retrospectively registered on 28 October 2016).

## Background

Ventilator-associated pneumonia (VAP) is a frequent complication of mechanical ventilation in the Intensive Care Unit (ICU) [1–3] and the associated morbidity results in substantial healthcare costs [4, 5]. The diagnosis of VAP remains challenging as clinical, laboratory and radiological parameters are sensitive but non-specific for VAP and suffer from high inter-rater variability [6, 7]. A lower respiratory tract sample [bronchoalveolar lavage (BAL), endotracheal aspirate or protected specimen brush sample] is recommended for microbiological confirmation of clinically suspected VAP [8], but these results take days to become available and the procedures cannot be repeated frequently due to their invasiveness. As a result of this delay, patients are overtreated with antibiotics, as empiric antibiotic treatment is initiated immediately after obtaining a lower respiratory tract sample. Subsequent microbiological results help to tailor and deescalate antibiotic treatment [9], so the lower respiratory tract sample continues to be of crucial importance for diagnosing VAP.

There is need for a less invasive and more time-efficient diagnostic technique that ultimately reduces the amount of antibiotics used to treat suspected VAP. Clinical scoring systems, like the Clinical Pulmonary Infection Score (CPIS) [10] and biomarkers have been studied as means to exclude VAP, but so far these attempts have not resulted in a test that is suitable for current ICU practice [11–15].

Exhaled breath contains volatile organic compounds (VOCs); small volatile molecules that result from host or bacterial metabolism or are contaminants from the environment [16, 17]. Exhaled VOC profiles have been shown to differentiate between many different disease states and may therefore qualify as non-invasive biomarkers [18–21]. Capture of VOCs and exhaled breath analysis has proven to be safe and reliable in mechanically ventilated critically ill patients [22–24]. Data from in-vitro experiments suggest that the presence of bacteria may be detected based on a small panel of VOCs [17]. This concept was recently translated in vivo: ventilated patients with and without positive bacterial cultures of endotracheal aspirate could be discriminated based on exhaled VOCs [24].

The aim of this study is to determine whether molecular analysis of breath can be used to discriminate between patients that are suspected of VAP who have positive cultures and who have negative cultures with high sensitivity, thus having the potential to limit antibiotic use. Secondly, we hypothesize that molecular analysis of breath can be used to specifically detect the causative pathogen in patients that are suspected of VAP, offering the possibility of more targeted antibiotic therapy.

## Methods

### Design

‘BreathDx – Molecular Analysis of Exhaled Breath as Diagnostic Test for Ventilator–Associated Pneumonia’ is an international European multicentre observational cohort study in intubated and ventilated ICU patients suspected of VAP. Six ICUs of university hospitals in the Netherlands, the United Kingdom, Spain and Portugal are involved: the Academic Medical Centre (AMC) in Amsterdam; University Hospital South Manchester (UHSM), Salford Royal and Central Manchester University Hospitals in Manchester; Parc Tauli Hospital in Sabadell; and Sao Francisco Hospital/Nova Medical School in Lisbon. Patients are expected to be recruited from all six sites over an 18 to 24-month time period. The project is funded by the European Union (*BreathDx – 611951*).

### Study population

Patients at one of the six involved ICUs that are clinically suspected of having VAP are eligible for the study. VAP is defined by (1) systemic changes [temperature >38 or <36.5 °C; white blood cell count <4,000 or >12,000/mm^3^]; and (2) chest abnormalities [new infiltrates on chest X-ray, purulent tracheal secretions]; and (3) positive microbiology results [25]. Inclusion criteria are (1) 18 years and older and (2) intubation and mechanical ventilation for > 48 h and (3) clinical suspicion of VAP (aforementioned systemic changes combined with chest abnormalities). Exclusion criteria include patients who: (1) are deemed clinically inappropriate to collect samples from (e.g. if they are receiving end-of-life care); or (2) are in strict isolation (e.g. Middle East Respiratory Syndrome, Ebola or resistant tuberculosis).

### Study procedures

Patients will be recruited and samples collected within 24 h of the clinical suspicion of VAP. First breath samples will be collected, followed by bronchoscopy and bronchial lavage. Standard Operating Procedures (SOPs) will be in place at all sites in order to ensure samples are collected equally. Breath samples will be shipped within days after collection and shall be analysed within 2 weeks upon arrival. Previous results have shown breath samples can be stored for at least 14 days without loss of data [26]. The (mini) BAL samples are processed and frozen immediately after recruitment. When all (mini) BAL samples are collected they will be shipped on dry ice to remain conserved.

### Breath sampling

Breath samples will be collected once (at time of recruitment) using a breath gas sampler (BGS, see Fig. 1) consisting of a pump (NMS020B 6VDC Micro Membranegas pump), a mass flow controller (Horiba STEC Z500), battery and charger (Panasonic LC-RA1212PG and IDEAL POWER PC170-2) all combined in a metal casing with operating display (Brooks Instrument 0254). Using this BGS and PTFE (PolyTetraFluoroEthylene) tubing (Swagelok, Warrington, UK), the exhaled breath is drawn from the sidearm of a T-piece connector inserted in the ventilator circuit distal of the HME filter and through a stainless steel sorbent tube (Markes International, Llantrisant, UK; and Gerstel, Mülheim an der Ruhr, Germany), adapted from Bos et al [23]. Subsequently the sorbent tubes will be transported for off-site analysis. The samples will be link-anonymised. Two pairs will be collected per patient and will be sent to two different laboratory locations for analysis (one pair to Philips Research, Eindhoven, the Netherlands and the other to Manchester Institute of Biotechnology, University of Manchester, Manchester, United Kingdom). For analysis at Philips Research the exhaled breath is collected using sorbent tubes packed with 300 mg Carbograph 5TD (Markes International, Llantrisant, UK) and 90 mg Tenax GR (Sigma-Aldrich Chemie B.V., Zwijndrecht, the Netherlands). The samples to be analysed at the Manchester Institute of Biotechnology are collected using sorbent tubes packed with 200 mg Tenax GR (Markes International, Llantrisant, UK). All samples are taken in duplicate. Breath samples are stored in a cold room immediately after collection. This sampling setup has shown to be safe and adequate for sample collection in ventilated ICU patients [18, 23, 27].

**Fig. 1 Fig1:**
[figure not shown]
The breath gas sampler

### Bronchoalveolar lavage

A (mini)-BAL sample will be obtained for microbiological analysis as soon as possible after collecting the breath samples (see Fig. 2). A syringe is connected to a bronchoscope or a 50 cm suctioning catheter and 20 mL 0.9% saline is injected in the airway. At least 4 mL is aspirated of which 1 mL is sent to the medical microbiology for routine cultures, leading to a semi-quantitative bacterial count with a cut-off of 10^4^ colony forming units/mL defining a positive culture. An aliquot of the (mini)-BAL sample will be processed and stored for future analysis.

**Fig. 2 Fig2:**
[figure not shown]
Overview of the sample collection

### Gas chromatography and mass-spectrometry

The exhaled breath sample will be analysed using Thermal Desorption – Gas Chromatography – Mass-Spectrometry (TD-GC-MS). In order to separate, quantify and identify a wide range of volatiles in breath, different chromatographic set-ups at Eindhoven and Manchester are used. Both GC-MS analyses will result in a list of detected volatiles and their relative concentrations.

At Philips Research, the sorbent tubes are thermally desorbed at 225 °C (TDSA, Gerstel, Mülheim an der Ruhr, Germany) into the GC capillary column. Solvent venting mode is used to transfer the sample without loss to the packed liner (filled with Tenax TA) held at −55 °C which is subsequently heated to 280 °C. A cold trap (CTS2, Gerstel, Mülheim an der Ruhr, Germany) is used to minimize band broadening (initial temperature −150 °C, after 1.6 min heated to 220 °C). A capillary gas chromatograph (6890 N GC, Agilent, SantaClara, CA, USA) using a VF1-MS column (length 30 m × internal diameter 0.25 mm, film thickness 1 μm, 100% dimethyl-polysiloxane, Varian Chrompack, Middelburg, the Netherlands) is used with the following temperature program: 30 °C-hold 3.5 min, ramp 5 °C/min to 50 °C, hold 0 min, ramp 10 °C/min to 90 °C, ramp 15 °C/min to 130 °C, ramp 30 °C/min to 180 °C, ramp 40 °C/min to 280 °C, hold 1 min. A Time-of-Flight Mass Spectrometer (Pegasus 4D system, LECO, St. Joseph, Mi, USA) is used in the electron ionization mode at 70 eV, with a scan range of m/z 29–400 Da, scanning rate 20 scans/s. Gaseous calibration standards (10 ppmv acetone-D8, hexane-D14, toluene-D8, xylene-D10 in nitrogen, Air Products, Amsterdam, the Netherlands) are made by use of a home-built dilution system and loaded on adsorption tubes as an internal standard.

At Manchester Institute of Biotechnology sorbent tubes filled with Tenax GR are thermally desorbed at 280 °C (TD100, Markes International, Llantrisant, UK) into a cold trap to minimize band broadening (initial temperature −0 °C, after 2 min heated again to 280 °C). This will then be fed into a capillary gas chromatograph (7890B GC, Agilent, SantaClara, CA, USA) using a HP-5 ms Ultra Inert column (length 30 m × internal diameter 0.25 mm, film thickness 0.25 μm, (5%-Phenyl)-methylpolysiloxane, Agilent, SantaClara, CA, USA) with the following temperature program: 40 °C - hold 0 min, ramp 6 °C/min to 170 °C, hold 0 min, ramp 15 °C/min to 190 °C for a total time of 23 min. A Triple-Quad mass spectrometer (7010, Agilent, SantaClara, CA, USA) will be used in the electron ionization mode at 70 eV, with a scan range of m/z 40–500 Da, scanning rate 4 scans/s. A gaseous calibration standard (1 ppmv, 4-Bromofluorobenzene in nitrogen, Thames Restek, UK) will be loaded on adsorption tubes as an internal standard for 1 min at 20 ml/min. Additionally, to aid in retention time correction, an external standard containing a mixture of laboratory standard VOC chemicals (Sigma Aldrich, UK) will be sampled on separate tubes, either side of a breath sample.

### Clinical data

Clinical data regarding patient characteristics, primary and secondary diagnoses, comorbidities, drug history, measures of disease severity such as Acute Physiology and Chronic Health Evaluation (APACHE) IV [28] and Simplified Acute Physiology Score (SAPS) II [29] ventilation data, CPIS [10], culture data, outcome variables (ICU/hospital length of stay, mortality) and adverse events will be collected.

### Study outcomes

The primary endpoint is the accuracy of cross-validated prediction for positive respiratory cultures in patients that are suspected of VAP, with a sensitivity of at least 99% (high negative predictive value).

The secondary endpoints are: (1) the accuracy of cross-validated prediction for growth of a specific pathogen with a specificity of at least 90%; (2) GC-MS identified molecular markers that can distinguish between patients with and without microbiologically confirmed VAP with *p* <0.05 and a false discovery rate <0.05; (3) GC-MS identified molecular markers that can distinguish between patients with and without growth of specific pathogens during bacterial culture with *p* <0.05 and a false discovery rate <0.05; (4) accuracy of prediction within the subgroup of patients with and without a previous respiratory infection; (5) accuracy of prediction within the subgroup of patients intubated for less and more than 1 week.

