### Sample size calculation

The sample size calculation has been performed based on binomial distributions instead of normal approximations to this distribution [30]. With an expected sensitivity of 99% (almost 100% negative predictive value) we require the lower 95% confidence limit to be larger than 90% with 95% probability. 90% sensitivity is the absolute minimal in a discovery study such as this, for a lower sensitivity is clinically irrelevant and would not be clinically useful. With these figures, the required number of cases is estimated to be 61 [30]. Assuming a prevalence of 40% of positive cultures of bronchoalveolar lavage in patients that are clinically suspected of VAP [24], the total study sample size should be 153 subjects.

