## Discussion

This manuscript describes the protocol for a multicentre prospective observational study that aims to develop a diagnostic tool for discriminating between patients that are suspected of VAP who have positive cultures and who have negative cultures through breath analysis using TD-GC-MS. Additionally, we aim to describe patterns of VOCs in exhaled breath that are predictive of the presence of specific pathogens. Ultimately we strive for a diagnostic test with 99% sensitivity for culture positive VAP, which is required in an ICU setting where delayed initiation of adequate antibiotic therapy is unacceptable.

Several clinical challenges can be recognized for this study a priori. First, the reported incidence of VAP has declined over the last decade [40]. As recruitment depends on the clinical suspicion of VAP, this could slow the inclusion rate. The clinical definition for inclusion into the study could also be seen as a weakness of the study as clinical practice may vary from hospital to hospital. However, we have tried to include hospitals from a wide variety of settings and countries throughout Europe to cover the heterogeneity in clinical practice. This geographical variation may also introduce noise into the data collected by breath analysis as the environment contributes to exhaled VOCs [41, 42]. Another challenge concerns the secondary aim of this study to identify patterns of VOCs that are predictive of the presence of specific causative pathogens. A number of VOCs are already associated with certain pathogens. There is a large number of pathogens that can cause VAP [43] and the groups of patients are not likely to be infected with the same pathogen. This is a risk that is inherent to a prospective clinical study. We expect to find sufficiently large groups of patients for at least the most important pathogens in VAP: *Pseudomonas aeruginosa*, *Staphylococcus aureus* and *Enterobacteriaceae* [43].

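### The primary endpoint asks for a sensitivity of at least 99%, the sample size is built only to exclude 90%, and nothing reconciles the two

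*Protocol article*

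**What the plan says.** Under Study outcomes, and in the same terms in the Abstract (Methods/design), the primary endpoint is the accuracy of cross-validated prediction of positive respiratory cultures "in patients that are suspected of VAP, with a sensitivity of at least 99% (high negative predictive value").

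The Sample size calculation treats 99% differently. It starts "With an expected sensitivity of 99% (almost 100% negative predictive value") and continues "we require the lower 95% confidence limit to be larger than 90% with 95% probability". It defends the lower figure: "90% sensitivity is the absolute minimal in a discovery study such as this". The method is exact: "The sample size calculation has been performed based on binomial distributions instead of normal approximations to this distribution". The result is that "the required number of cases is estimated to be 61", and at a prevalence of 40% this becomes 153 subjects. Whether the 95% limit is one- or two-sided is not stated.

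The Abstract (Discussion) says "BreathDx is the first study powered to investigate whether molecular analysis of breath can be used to classify suspected VAP patients", and the sentence goes on to name 99% sensitivity. The Discussion says "Ultimately we strive for a diagnostic test with 99% sensitivity for culture positive VAP, which is required in an ICU setting". Its paragraph on clinical implications makes the practical conclusion conditional on 99% being attained, and also refers to 99% as a sensitivity selected beforehand.

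**The concern.** Taken at face value, 99% is a required result in one section and a planning assumption in another, where the required result is a confidence limit above 90%. One data set could then be judged in two ways. With 60 of 61 culture-positive patients detected, the sample-size rule is met, but the observed sensitivity is below the figure in the endpoint.

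What is at stake is how the primary result is described. The claimed use is rule-out, and the gap between 99% and 90% is large for that purpose. At the Discussion's own 40% prevalence and 80% specificity, the negative predictive value is 0.480/(0.480 + 0.004) = 99.2% at a sensitivity of 99%, and 0.480/(0.480 + 0.040) = 92.3% at 90%. False negatives number 4 and 40 per 1,000 suspected patients respectively. The remark in the Sample size calculation about a negative predictive value close to 100% holds at the expected sensitivity, not at the limit that the study is sized to exclude. As the text stands, a result that only excludes 90% could be reported as a 99% rule-out test.

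**Working it through.** **Inputs.** From the Sample size calculation: expected sensitivity 0.99, value to exclude 0.90, 95% confidence limit, 95% probability, exact binomial method, 61 cases, 40% prevalence, 153 subjects. From Study outcomes: sensitivity of at least 99%.

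**1. Reproducing the plan's figure.** Find the smallest n for which the exact (Clopper-Pearson) one-sided 95% lower limit exceeds 0.90 with probability at least 0.95 when the true sensitivity is 0.99.

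- n = 60: at most 1 miss is allowed, and the probability is 0.879.
- n = 61: at most 2 misses are allowed. P(0) + P(1) + P(2) = 0.5417 + 0.3338 + 0.1011 = 0.977.

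So n = 61, and 61/0.40 = 152.5, rounded up to 153. Both figures reproduce. If the true sensitivity were 0.90, the chance of at most 2 misses in 61 would be 0.049.

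**2. What each outcome would mean with 61 cases.**

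| Detected | Observed sensitivity | One-sided 95% lower limit | Meets sizing rule (limit > 90%) | Observed at least 99% |
|---|---|---|---|---|
| 61/61 | 100% | 95.2% | yes | yes |
| 60/61 | 98.4% | 92.5% | yes | no |
| 59/61 | 96.7% | 90.04% | yes | no |
| 58/61 | 95.1% | 87.8% | no | no |

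An observed sensitivity of at least 99% requires no misses, because one miss is compatible with 99% only from 100 cases upward. The lower limit for 61/61 is 0.05^(1/61) = 0.952.

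**3. Probabilities if the true sensitivity is 99%.** The sizing rule is met with probability 0.977. An observed value of at least 99% occurs with probability 0.99^61 = 0.542. The 95% probability in the Sample size calculation therefore belongs to the 90% criterion alone.

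**4. Sidedness.** With a two-sided 95% exact interval (lower tail 2.5%), the lower limit for 59/61 is 88.7%. Only 0 or 1 miss then qualifies, so the probability at n = 61 is 0.5417 + 0.3338 = 0.875. The 95% target is first met at n = 70, and at every n from 85 on. Of the exact and Wilson limits tried, one- and two-sided, only the one-sided exact limit gives 61 as the smallest n.

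**The case against.** The strongest reply is that the endpoint states no pass mark. Grammatically the endpoint is accuracy, and the 99% clause fixes the operating point at which accuracy is judged. The first secondary endpoint has the same form, with a specificity of at least 90%, and the Discussion speaks of a sensitivity chosen in advance. On that reading 60/61 fails nothing. This is plausible, but it does not remove the mismatch. If sensitivity is set by the choice of cut-off, what remains to be estimated is specificity or accuracy, whereas the Sample size calculation treats sensitivity as the free proportion. Under either reading endpoint and sizing differ, and the text does not say which reading applies.

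Other parts of the reply stand:

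- Different planning and null values are normal in a power calculation. The 90% floor is disclosed and justified.
- The Abstract claims power to investigate whether classification at 99% is possible. Power is computed at an assumed true value, here 99%, and is 97.7%. The sentence is loose, not false.
- The Discussion's remark that 99% is required describes the test ultimately aimed for, not what this discovery study must prove.

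A reader might infer that the study is too small. The documents do not support this, since no section asks for a lower limit above 99%. The 299 cases without a miss needed for that (ln 0.05/ln 0.99, rounded up; about 748 patients at 40% prevalence) are illustrative only. Nor is 54% a power shortfall. It is the chance that an estimate reaches its own true value, and at 299 cases that chance is 42%.

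**Conclusion.** The concern holds as an unreconciled pair of criteria, not as an error in the sample size. The endpoint names at least 99%, while the design gives 97.7% assurance of excluding 90% if the true sensitivity is 99%. Two possible results, 59/61 and 60/61, satisfy the second and fall below the first. The best possible result, 61/61, supports a sensitivity above about 95.2% (one-sided), so the design cannot establish 99%. The Abstract's statement on power and the Discussion's conditional conclusion need qualifying for that reason.

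This rests on exact binomial limits, on exactly 61 culture-positive cases being obtained, and on treating the cross-validated classifications as independent at a pre-set cut-off. It matters because it decides how the primary result may be described, so it should be settled before the data are analysed.

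**What to change.** - **Study outcomes and Abstract (Methods/design):** state one criterion. For example: cross-validated sensitivity at the pre-set cut-off, with success if its one-sided exact 95% lower confidence limit exceeds 90%; 99% is the planning value or target operating point.
- **Sample size calculation:** say that the 95% limit is one-sided. If a two-sided 95% interval is intended, 61 cases give only 87.5% assurance and the number must be revisited.
- **Abstract (Discussion):** replace the statement on power with wording such as: sized so that, if true sensitivity is 99%, a sensitivity of 90% or lower can be excluded.
- **Discussion:** qualify the conclusion that depends on 99% being attained so that it matches the chosen criterion, and reconcile the description of 99% as required with the 90% minimum accepted for this study.

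The cost is wording only. With the one-sided limit, sample size, data and analysis stay as they are; the downside is a less favourable stated claim.
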